#### Covariates

The autonomic nervous system is responsible for maintaining homeostasis and regulates processes such as blood pressure,^36^ digestion,^37^ metabolism^38^ and circadian rhythm,^39^ all of which may affect cardiac function and show as changes in the ECG morphology.^40–43^ Additionally, exercise can affect the QT interval, that is the ECG section representing ventricular depolarisation, due to exercise-induced autonomic response.^44^ During phase 1 of the study, daytime blood pressure will be monitored, and the calorific value and macronutrient composition of meals will be recorded. Additionally, exercise sessions will be scheduled throughout the phase. Throughout the free-living phase, all meals, exercise duration and intensity, and sleep times will be recorded by the participant. The data collected via this protocol enable us to examine how the covariates relate to the outcome of interest, that is, the glycaemic status, by performing statistical tests such as analysis of variance.^45^ The recording of mealtimes, exercise and sleep enables the data to be analysed during distinct periods of interest such as post-exercise or postprandial.

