## Methods and analysis

### Study setting

This two-phase observational study will be conducted at the Human Metabolism Research Unit (HMRU) and in free-living conditions. During phase 1, the participants attend an inpatient protocol at University Hospital Coventry and Warwickshire (UHCW) in a calorimetry room for up to 36 hours. The calorimetry room is a controlled environment, which allows for precise regulation of parameters such as ambient temperature, air pressure, humidity and subject behaviour enabling us to obtain high-quality baseline ECG and glucose data from the wearable sensors. In phase 2, the same sensors will be used to collect data under free-living conditions, for a period of up to 3 days, during which the participants are free to go about their normal daily activities without restriction. Participants will be asked to complete diaries for daily activity, food intake and sleep.

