### Sample size

As this is an observational study, an exact sample size calculation is not possible. A target of 30 participants will be enrolled, based on a pragmatic approach, which ensures sufficient data are available for analysis. Full participation in the protocol will yield 108 hours of continuous data per participant. We aim to capture the daily blood glucose fluctuations known as glycaemic variability,^27^ a feature of impaired glucose metabolism. However, it is not possible to anticipate how many hypoglycaemic episodes will be recorded. ECG data, labelled with corresponding glucose concentration, will be analysed in excerpts of variable length from individual heartbeats (cardiac cycles) to several minutes, resulting in a large sample size.

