### Study protocol

#### Calorimetry room

The participant will stay in the calorimetry room for up to 36 hours, during which there will be set times for meals, light exercise and rest. Meals will be provided with known total energy and macronutrient content. Water will be provided ad libitum. While in the calorimetry room, wearable sensors will record physiological data continuously.

Other activities will be performed during this time, specifically: (a) up to 12 serial blood samples of 30 mL will be obtained from a peripheral venous catheter inserted at the beginning of phase 1 to measure venous glucose and insulin concentration, (b) finger-prick blood samples will be taken periodically for capillary glucose measurements, (c) up to 12 saliva samples will be taken to analyse salivary concentration of cortisol and melatonin, (d) all urine will be collected as voided for protein oxidation analysis, (e) movement and activity will be assessed by motion sensors, (f) simple questionnaires will be used to measure food intake and activity as well as subjective aspects such as appetite, satiety and wellness, and (g) daytime blood pressure will be monitored using an ambulatory blood pressure monitor (hourly readings).

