#### Data analysis

Data will be obtained from several days of continuous physiological monitoring of participants. During analysis, the data will be divided into smaller excerpts such as 1, 2 or 5 min intervals. In addition, beat-level ECG samples will be analysed; therefore, the total number of samples available during analysis is ambiguous.

Characteristics of an ECG can be represented by heart rate variability (HRV) parameters and can be categorised into time-domain features, frequency-domain features and non-linear features.^33^ We aim to use physiological signal processing packages such as NeuroKit2^34^ and HeartPy^35^ to determine these features. Furthermore, we aim to determine ECG beat parameters, which include length and slope among the fiducial points (P, Q, R, S and T). We will perform statistical tests to determine the statistical significance of different HRV features and ECG morphology parameters among different glycaemic values to determine which parameters are associated with hypoglycaemia.

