The study will add to the body of evidence evaluating AI for use in the detection of glycaemic events (eg, hypoglycaemia) in free-living conditions. Current efforts in the literature have been limited by small sample sizes,^48^ healthy subject populations^16^ and data originating from highly controlled experimental settings.^49^ This study protocol has been developed to address the gaps of the existing literature. As such, the strengths of this study design are that data are collected from participants with diabetes, both in controlled and free-living settings. An additional strength of this protocol is that it has been designed with non-compliance in mind. The first phase will take place in a metabolic chamber where the activities of the participants and the operation of the wearable sensors are prescriptive and supervised. This enables us to obtain high-quality baseline data. The second phase will take place in free-living conditions where the participants go about their normal daily activities unencumbered by the wearable sensors, providing real-life data. During the free-living phase, a level of non-compliance and variance is desirable in order to determine how our analysis and model work with real-world data. Non-compliance with the protocol will not exclude the participant from inclusion in the analysis. Any deviations from the protocol will be noted. Participation in both phases of the study is not a requirement; therefore, we are likely to obtain different number of samples for each participant. We will take a pragmatic approach and work with the data available at the end of the study. All analyses will report the number of samples used and if excerpts of data have been excluded and for what reason. Our planned analysis will segment the continuous physiological data into smaller excerpts of variable length, yielding a sufficient sample size for the training algorithm to discover relevant features in the data.

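### Beats and short excerpts from at most 30 people are counted as a large sample, and nothing makes the participant the unit of inference for the planned association tests

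*Protocol article*

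**What the plan says.** The Sample size section gives no calculation: "A target of 30 participants will be enrolled, based on a pragmatic approach". It adds that "Full participation in the protocol will yield 108 hours of continuous data per participant", and that the labelled ECG data "will be analysed in excerpts of variable length from individual heartbeats (cardiac cycles) to several minutes, resulting in a large sample size".

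The Data analysis section uses the same units (excerpts of 1, 2 or 5 minutes, and single beats) and calls the total number of samples ambiguous. It then announces: "We will perform statistical tests to determine the statistical significance of different HRV features and ECG morphology parameters among different glycaemic values". The aim is to find which parameters go with hypoglycaemia. Neither the test nor its unit is named.

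The Covariates section will examine how covariates relate to "the glycaemic status, by performing statistical tests such as analysis of variance". The form of the analysis of variance is not given.

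Under Data processing, glucose reported every 15 minutes is interpolated linearly to every second, and beats are grouped into 15-minute excerpts for annotation. Under Data modelling, the prediction model is tested by subject-wise cross-validation. For the association tests, the article mentions no participant effect, repeated-measures structure or serial correlation.

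**The concern.** The independent units are the participants, and within each one the distinct glycaemic episodes. Beats from one person share that person's ECG characteristics. Neighbouring excerpts resemble each other, and so do neighbouring glucose values. Cutting the same recording more finely raises the row count but adds no information on glycaemia. Between two sensor readings, every interpolated value derives from those same two readings.

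The article presents the row count as the sample size. A test that takes this at face value uses a standard error that is much too small. Determining how ECG-derived features relate to glycaemic status is part of the stated primary objective, so unrelated features could be reported as markers of hypoglycaemia. If features were also screened by such tests on all the data before modelling, the screening could leak into the cross-validation. The article does not say that this will be done.

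**Working it through.** **1. The article's own figure.** Phase 1: "The participant will stay in the calorimetry room for up to 36 hours". Phase 2: "for a period of up to 3 days, during which the participants are free to go about their normal daily activities". Hence 36 + 3 × 24 = 108 hours, which agrees with the article.

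**2. Rows against readings.** For 30 full participants:
- Glucose readings: 108 × 4 = 432 each, 12,960 in all.
- 5-minute excerpts: 108 × 12 = 1,296 each, 38,880 in all.
- 1-minute excerpts: 108 × 60 = 6,480 each, 194,400 in all.
- Beats at an assumed 70 per minute: 6,480 × 70 = 453,600 each, about 13.6 million in all.

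These are maxima, since participants may enrol in one phase only.

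**3. Formulae.** If variance is understated by a factor D, a nominal 5% z-test has type I error 2 × [1 − Φ(1.96/√D)]. This exceeds one half once D passes about 8.4.
- *Clustering, upper-end case with exposure constant within a person:* D = 1 + (m − 1) × ICC. For 5-minute excerpts and ICC 0.1, D = 1 + 1,295 × 0.1 = 130.5. The effective number is 38,880/130.5 ≈ 298 and the error is 0.86. With ICC 0.01, D ≈ 14 and the error is 0.60.
- *Serial correlation only:* D = (1 + r)/(1 − r), where r is the product of the lag-one correlations of feature and glucose. Take time constants of 30 minutes (feature) and 90 minutes (glucose). At 15 minutes r = exp(−15/30 − 15/90) = 0.513, D = 3.1 and the error is 0.27. At 5 minutes r = 0.801, D = 9.0 and the error is 0.51. At 1 minute r = 0.957, D = 45 and the error is 0.77.

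**4. Simulation with no true association.** There were 30 participants × 108 hours. Glucose was first-order autoregressive with a 90-minute time constant, participant means 9 (SD 1.5) mmol/L and within-participant SD 3 mmol/L. Three states were cut at 3.9 and 11.1 mmol/L, the article's Table 1 limits. There were 400 runs per setting (150 for 1-minute excerpts). Alpha is not stated, so 5% is assumed.

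| Analysis | 15 min | 5 min | 1 min |
|---|---|---|---|
| Pooled ANOVA, no dependence | 5% | 4% | 7% |
| Pooled, serial correlation only (30–60 min) | 30–43% | 66–70% | 87–97% |
| Pooled, ICC 0.1–0.5, serial correlation 0–60 min | 48–84% | 71–95% | 93–98% |
| Centred on participant, all settings with serial correlation | 14–39% | 45–77% | 85–95% |
| Contrast per participant, t-test across participants | 4–6% | 3–7% | 3–8% |

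The simulation error (one SE) at a true 5% is √(0.05 × 0.95/400) = 1.1 points, or 1.8 points with 150 runs. The last row is therefore compatible with 5%. With only 10 or 20 participants and 5-minute excerpts, the contrast rejects in 2–5% and the pooled test in 77–93%.

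**5. Sensitivity to assumptions.** A second set used a glucose correlation time of 2 hours, ICC 0.1–0.5, a feature correlation time of 15–60 minutes and 30–70% white noise. Pooled ANOVA rejected in 51–84%, 79–95% and 95–99% for 15, 5 and 1 minutes. Participant-centred data gave 6–31%, 19–65% and 59–91%. The contrast gave 1–6%.

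**The case against.** The article does not say that ordinary ANOVA will be run on excerpts. It names ANOVA only for covariates, gives no variant, and leaves the ECG-feature tests unnamed. A repeated-measures or mixed form is not excluded, and a fuller plan may specify one. Test variant, covariate adjustment and multiplicity control are details that an article commonly leaves out. The Discussion's statement on segmentation, "yielding a sufficient sample size for the training algorithm to discover relevant features in the data", concerns training and not hypothesis tests. Subject-wise cross-validation keeps participants separate when the model is validated.

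All of this stands, and it limits the point. A reader might infer that the plan has chosen independent-observation ANOVA for the ECG features and that most unrelated features will therefore appear significant. The text does not support that. The form of test is unstated, and with 15-minute excerpts, the length used for annotation, false rejection can lie below one half (30–48% at the low end). Nor does the article say that the feature tests are unadjusted: it records meals, exercise and sleep and foresees analysis by period. Labels between two glucose readings need not be identical either, since interpolated glucose can cross a threshold.

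The Sample size statement is not answered by this. It is a positive claim about the amount of information, the Data analysis section adopts the same units just before announcing significance tests, and the participant is respected only in the prediction model.

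**Conclusion.** The point holds in conditional form. The article's stated sample basis is wrong for inference, and nothing in it makes the participant the unit for the association tests. If those tests follow the stated basis, type I error at a nominal 5% is about 50–85% with 15-minute, 70–95% with 5-minute and 93–99% with 1-minute excerpts, given ICC 0.1–0.5 and serial correlation up to 60 minutes. With serial correlation only, 15-minute excerpts give 30–43%. The ICC, correlation times and glucose distribution are assumptions, but two different sets agree closely for the pooled tests. Removing participant means is not enough when the feature is serially correlated. Validation of the prediction model is not affected, unless features are first screened on all the data.

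**What to change.** **Data analysis and Covariates sections:** state that the participant is the unit of inference for the association tests, and use one of the following.
- A linear mixed model with glycaemic state as predictor, participant random intercept and slope, and serially correlated residuals.
- For each feature, one mean difference per participant (hypoglycaemia minus euglycaemia), tested across participants. This is undefined for anyone without hypoglycaemia, so report how many participants contribute. The article itself says the number of episodes cannot be foreseen.

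**Sample size section:** for these tests, replace the claim of a large sample by the number of participants and of distinct hypoglycaemic episodes.

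False discovery rate control across features, and activity and sleep/wake as covariates, are sensible additions. Adjustment for RR interval belongs in a sensitivity analysis: HRV features derive from RR, and autonomic change may be part of the pathway under study.

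**Cost:** a change of wording and a little more code, with no new data. Intervals will be wider and fewer features will be declared significant.

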#### Data modelling

The inherent part of the project is to develop AI models for detecting glycaemic events and inferring them with physical activity and diet. The state-of-the-art AI models vary from traditional machine learning models (such as Support Vector Machines, Decision Trees, etc) to advanced deep learning-based models.^46^ Traditional machine learning models have the capability to train static features for the development of explanatory models, whereas deep learning models can train raw ECG signals based on spatial and temporal context. The deep learning models will be built upon earlier work developed for healthy subjects.^15^ We aim to develop and validate hypoglycaemia detection models that incorporate lifestyle trends such as activity levels and sleep patterns using metrics provided by the sensors and reported in the diaries. For a model to be clinically useful, it should demonstrate generalisability. Therefore, we will test the model on unseen data using a subject-wise cross-validation approach.^47^

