The self-monitoring of blood glucose (SMBG) can play a key role in effective management of diabetes. SMBG can empower patients to adhere to lifestyle interventions, such as changes to diet and exercise regimen, as they have access to immediate feedback on the effects.^8^ Active participation from the patient in their care has been shown to improve outcomes such as reducing the risk of diabetic complications.^9^ Current methods for glucose monitoring have several limitations. The most common method for SMBG is an invasive ‘finger-prick test’ in which a small sample of blood is collected from the fingertip and analysed by a handheld device called a glucometer. This invasive procedure has several documented barriers preventing SMBG such as inconvenience, cost and discomfort.^10^ Moreover, the devices and associated consumables are prone to error if not operated correctly,^11^ requiring repeat attempts and generating unnecessary waste. Hypoglycaemia typically occurs during sleep,^12^ and those receiving insulin therapy are at increased risk due to a combination of factors such as impaired counter-regulatory hormone response and warning symptoms going unobserved.^13^ This presents an obvious limitation to the effectiveness of an invasive ‘finger-prick test’ as a tool for SMBG. An alternative to ‘finger-pricking’ are continuous glucose monitoring (CGM) devices, which require a small cannula inserted in the top layer of skin to continuously measure glucose in the fluid between the cells. They can be described as minimally invasive as after the initial fitting, they are routinely worn continuously for up to 14 days. However, despite being shown to be a beneficial tool for SMBG, national clinical guidelines for the UK do not recommend routine use of CGM devices for the management of T1DM due to insufficient evidence demonstrating their efficacy and cost-effectiveness.^14^

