It has been demonstrated, by this group^15 16^ and others,^17–19^ that glycaemic events can affect certain cardiac characteristics, which can be extracted from readings of the electrical activity of the heart, the ECG. With increasing availability of wearable devices for tracking physiological signals, studies have been undertaken to investigate prediction of blood glucose concentration or glycaemic event detection using artificial intelligence (AI), by combining data or features extracted from the ECG with blood glucose measurements. Such an approach would address the need for non-invasive continuous blood glucose monitoring. Studies have shown promising predictive performance based on data collected from healthy subjects^15 16 20–22^ or adolescent patients with T1DM.^19 23^ In a review of techniques for detecting hypoglycaemia, Diouri *et al* note that the use of ECG-based techniques has only been investigated in small cohort trials, and that the success of such approaches relies on further, ideally larger, trials and validation in patients with diabetes and cardiac diseases.^24^

This protocol expands on an initial pilot, results of which are published,^15^ which made opportune use of applicable secondary data collected for a separate study^25^ on healthy elderly men. The aim of the pilot was to use the data to create a personalised AI model for the detection of nocturnal hypoglycaemia. The developed and validated deep learning model achieved 90% for specificity (ability to identify true positives) and sensitivity (ability to identify true negatives), which are clinically relevant metrics in relation to diagnosis of disease.^26^ The aim of this protocol is to build on this initial work, by obtaining new data to validate the technique for people with diabetes and test its applicability beyond controlled conditions, to that of normal living conditions.

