#### Primary objective

The primary objective of this study is to further develop and validate in a new population (T1DM) our previously developed AI approaches for non-invasive hypoglycaemia detection. We will extract and analyse ECG-derived features from the raw signal and determine their relationship with the glycaemic status. State-of-the-art algorithms will be used to create a mathematical mapping from the ECG-derived features to the glycaemic status.

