#### Secondary objective

To examine the impact of physical activity and diet on glycaemic events and incorporate relevant features into the model.

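### The validation stated under Data modelling cannot show that above-chance hypoglycaemia detection comes from glucose information in the ECG rather than from sleep or activity

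*Protocol article*

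**What the plan says.** The Primary objective section of the protocol article sets out to "create a mathematical mapping from the ECG-derived features to the glycaemic status". The Secondary objective is "To examine the impact of physical activity and diet on glycaemic events and incorporate relevant features into the model". The Discussion keeps this order, with exercise, diet and sleep as predictors under a secondary outcome.

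The Data modelling section states what will be built and tested: "We aim to develop and validate hypoglycaemia detection models that incorporate lifestyle trends such as activity levels and sleep patterns". It then says that the model will be tested on unseen data by subject-wise cross-validation. No other validation rule is given.

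Three other statements bear on how such a result can be read:

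- Introduction: "Hypoglycaemia typically occurs during sleep".
- Covariates: blood pressure, digestion, metabolism and circadian rhythm are listed as under autonomic control, "all of which may affect cardiac function and show as changes in the ECG morphology". Exercise is said to affect the QT interval.
- Calorimetry room: in phase 1, "there will be set times for meals, light exercise and rest".

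The Sample size section gives 108 hours of continuous data per fully participating patient. The Introduction describes the pilot's aim as to "create a personalised AI model for the detection of nocturnal hypoglycaemia" and reports 90% for both sensitivity and specificity.

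**The concern.** Sleep and time of day are, on the article's own account, associated with the label (hypoglycaemia) and with the predictor (ECG shape and rhythm). A detector trained on day and night recordings can therefore gain discrimination by recognising that a person is asleep, resting or recently active. It can do so through the activity and sleep inputs, or through the ECG itself.

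Subject-wise cross-validation protects against leakage between recordings of one person. It does not protect against a pattern that people share. If most participants sleep at night and hypoglycaemia is more frequent then, a model that has learned sleep will carry over to held-out participants.

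At stake is the claim that the study exists to support: that a wearable ECG carries usable information on glucose in T1DM. A moderate, above-chance result could be credited to the ECG when some or all of it reflects sleep or activity.

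**Working it through.** **Consistency of the recording time.** Phase 1 is up to 36 h and phase 2 up to 3 days: 36 + 3 × 24 = 108 h. This reproduces the figure in the Sample size section and confirms that the data cover days and nights.

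**Objective against validation.** The primary objective names ECG-derived features only. The models that Data modelling says will be developed and validated include activity and sleep. No sentence assigns one validated model to the primary objective and another to the secondary, or states a contrast between them.

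**Do other planned analyses separate ECG from sleep?**

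- Data analysis: heart rate variability and morphology parameters are tested across glycaemic values. No conditioning on sleep or activity is stated, so the same confounding applies.
- Covariates: covariates are related to glycaemic status. That does not show whether the ECG adds anything beyond them.
- Covariates, last sentence: recording meals, exercise and sleep is said to make analysis by period possible. The examples are post-exercise and postprandial periods. Nothing ties this to judging the detector.

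**How much could sleep alone contribute?** The article gives none of the three inputs needed, so all are assumptions:

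- f, the fraction of time asleep: 8/24 = 0.333
- p, the fraction of time hypoglycaemic: 0.04 to 0.05
- q, the share of hypoglycaemic time that falls in sleep: 1/3 to 0.9

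Consider the rule *flag if asleep*, with no ECG, judged over day and night together.

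- Sensitivity = q
- Specificity = 1 − (f − q·p)/(1 − p)
- AUC of a binary rule = (sensitivity + specificity)/2

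Worked case, q = 0.5 and p = 0.05: specificity = 1 − (0.333 − 0.025)/0.95 = 0.675, and AUC = (0.500 + 0.675)/2 = 0.588.

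| q | Sensitivity | Specificity (p = 0.05) | AUC (p = 0.05) | AUC (p = 0.04) |
|---|---|---|---|---|
| 1/3 (no sleep excess) | 0.33 | 0.67 | 0.50 | 0.50 |
| 0.5 | 0.50 | 0.68 | 0.588 | 0.587 |
| 0.7 | 0.70 | 0.69 | 0.693 | 0.691 |
| 0.8 | 0.80 | 0.69 | 0.746 | 0.743 |
| 0.9 | 0.90 | 0.70 | 0.798 | 0.795 |

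With 7 to 8 h of sleep, p from 0.03 to 0.08 and q from 0.5 to 0.9, the AUC runs from 0.59 to 0.83 and specificity from 0.67 to 0.76.

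Judged within sleep only, the rule flags every excerpt: sensitivity 1, specificity 0, AUC 0.50. The contrast between the overall and the within-sleep figure is what makes separate reporting informative.

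**Would leaving out the lifestyle inputs be enough?** Suppose an ECG-only model recognises sleep with accuracy a, in both sleep and wake, and carries no glucose information. With s = (f − q·p)/(1 − p), the share of non-hypoglycaemic time spent asleep, its balanced accuracy is 0.5 + (2a − 1)(q − s)/2.

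- a = 0.8, q = 0.5, p = 0.05: s = 0.325, giving 0.5 + 0.6 × 0.175/2 = 0.553
- a = 0.9, q = 0.8, p = 0.05: s = 0.309, giving 0.5 + 0.8 × 0.491/2 = 0.696

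So an ECG-only model can also score above chance, about 0.55 to 0.70 here, by encoding sleep. An ECG-only analysis is needed, but does not settle attribution by itself.

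**The case against.** The strongest objection is that this is largely silence. Comparator models and performance by period are details that a condensed article may leave to a full protocol or analysis plan that is not shown. That is fair, and the absence of a benchmark would be weak ground alone. What does not depend on it is the mismatch in the text: an ECG-only primary objective, and a stated validation of models that take in sleep and activity.

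A second objection is that sleep and activity are legitimate predictors if the aim is simply to detect hypoglycaemia. This also stands. Making the ECG's incremental gain the primary claim would change the study's question, so the gain should be reported alongside detection performance and not replace it.

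A reader might go further in several ways that the article does not support:

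- *The primary objective will go unanswered.* Raw-ECG models are planned, ECG parameters are tested against glycaemic values, and the objectives rank ECG first. The problem is attribution under the stated validation.
- *Performance will be pooled over day and night.* The article says how long data are collected, not how performance will be summarised, and it allows for analysis by period.
- *The fixed timetable drives the result.* Set times apply in phase 1 only, at most 36 of 108 h; phase 2 is unrestricted.
- *Sleep recognition could mimic the pilot's performance.* In no assumed case does the sleep rule reach 90% on both measures, because its specificity stays at 0.67 to 0.76.
- *The pilot was immune to this problem, or its 90% is the yardstick here.* The article gives the pilot's aim and headline result only, nocturnal is not the same as asleep, and the 90% is not set as a target for this study.

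**Conclusion.** The point holds as one of attribution. Followed as written, the Data modelling section yields a performance figure that cannot separate glucose information in the ECG from sleep or activity, and subject-wise cross-validation does not remove a day-night pattern common to participants.

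The size is uncertain. Under the assumptions above, sleep status alone gives anything from no discrimination (AUC 0.50, no sleep excess) to moderate discrimination (about 0.80, with 90% of hypoglycaemic time in sleep). The Introduction's statement on sleep points towards some excess but gives no share. The risk is that a moderate result is over-read. This is a cheap improvement to the plan and no ground for calling the design invalid.

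**What to change.** In the Data modelling section:

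1. Report the ECG-only model for the primary objective and the lifestyle-augmented model under the secondary objective.
2. In the same subject-wise folds, fit an ECG-free benchmark on clock time, sleep/wake, activity, posture, and meal and exercise timing. Report the gain from adding ECG to it, next to the detection performance.
3. Report detector performance separately for sleep and waking periods.

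The cost is a few sentences of analysis wording and one extra model per fold. The inputs are already collected through the chest sensor, the phase 1 schedule and the diaries. The downside is a possibly less favourable headline figure, and less precise estimates within each period, which matters because the Sample size section says that the number of hypoglycaemic episodes cannot be anticipated.
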